### Research Question and Objectives

The overarching research question for this study is as follows: Where do nursing and allied health professionals who have had a student placement in the NT end up practicing? The primary objective of this study is to identify the workplace locations, annually, of nursing and allied health students who completed an NT work-integrated learning placement; this will be conducted for 10 years postgraduation. The secondary objectives of this study are as follows: (1) investigate factors that contribute to work location decisions and (2) determine if and how an NT placement influenced career decisions.

## Methods

### Theoretical Framework and Study Design

The research will use a pragmatist theoretical framework [39-41]. This research is an observational cohort study with data collection occurring at baseline and repeated annually over 10 years, from 2017-2018 to 2029 (see Table 1). The baseline data collection includes a demographic profile of nursing and allied health students and their evaluations of their NT placements (ie, Survey 1: Student Satisfaction Survey). The Student Satisfaction Survey is used nationally by University Departments of Rural Health across Australia [42]. The annual survey (ie, Survey 2: Work Location Survey) has been purpose developed to track work location and the influences on work location decisions.

**Table 1 table1:** Study design showing timing of recruitment and data collection.

Participant cohort	Study activity by year				
	2020	2021	2022	2023-2028	2029
Retrospective recruitment of 2017-2019 students (Cohorts 1-3)	Access to Flinders University Northern Territory (NT) database of completed placements Recruit and obtain consent using last known phone number and email address Survey 1^a^: already undertaken as part of routine quality assurance Survey 2.1^b^	Survey 2.2	Survey 2.3	Survey 2 taken annually up to and including 2026 for Cohort 1 and up to and including 2027 for Cohort 2	Completed
Recruitment of 2020 students (Cohort 4)	Access to Flinders NT database of commencing placements Recruit and obtain consent when sent Survey 1	Survey 2.1	Survey 2.2	Survey 2 taken annually up to and including 2028	Completed
Recruitment of 2021 students (Cohort 5)	N/A^c^	Access to Flinders NT database of commencing placements Recruit and obtain consent when sent Survey 1	Survey 2.1	Survey 2.2	Survey 2 taken annually until 2029 Cohort 5 tracked for 8 years in the workforce
Recruitment of 2022-2027 students (Cohorts 6-11)	N/A	N/A	Access to Flinders NT database of commencing placements Recruit and obtain consent when sent Survey 1	Survey 2.1	Survey 2 taken annually until 2029 Cohort 6 tracked for 7 years in the workforce Cohort 7 tracked for 6 years in the workforce Cohort 8 tracked for 5 years in the workforce Cohort 9 tracked for 4 years in the workforce Cohort 10 tracked for 3 years in the workforce Cohort 11 tracked for 2 years in the workforce
Recruitment of 2028 students (Cohort 12)	N/A	N/A	N/A	Access to Flinders NT database of commencing placements Recruit and obtain consent when sent Survey 1	Survey 2.1

^a^Survey 1 is the Student Satisfaction Survey and is a student evaluation of their placement.

^b^Survey 2 is the Work Location Survey. Note that 2.1 refers to participants’ first year in the workforce or postgraduation, 2.2 is their second year, etc. Participation ends after 10 years in the workforce or postgraduation.

^c^N/A: not applicable; no study activities were performed in this year for these cohorts.

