### Sample Size

In 2017, Flinders NT supported 462 students on placement from more than 20 universities across Australia. The average response rate to the standard quality assurance Student Satisfaction Survey regarding placement is about 30%. Based on 450 students per year undertaking placements and a conservative 15% response rate in the first year from students in the first three cohorts, approximately 203 participants will be added in the first year. Each year, another 450 students will be added to the sampling pool; however, over a 10-year period, we assume that the response rate will decline logarithmically by 1% each year, so that in the tenth year the response rate will be 6%. This equates to a total possible pool of 5400 participants who will each be offered up to 10 surveys, depending on the year they commenced in the study; however, with the declining response rates, we anticipate a final sample of 3175.

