### Participant Recruitment

The recruitment process comprises an email invitation to participate. If a message bounces back from an email address, we will contact the participant seeking an email address via the last known telephone number in the database.

The research is comprised of annual online surveys, or phone surveys at the participant’s request. Survey 1 (ie, the Student Satisfaction Survey) is the first survey and is an evaluation of the student placement. The following year, Survey 2 (ie, the Work Location Survey) is sent, which comprises a 10-minute online survey asking about current work location and work location history and includes several questions regarding the influences on work location decisions. All subsequent years will use Survey 2 (ie, the Work Location Survey) to ask about work location and work location history, but this survey will not repeat the initial questions regarding demography and the NT placement.

Participation is voluntary and former students can also opt out of receiving any further surveys. In order to maximize the response rate while avoiding harassment of potential participants, we will send an email invitation to complete the survey, followed by two reminders that also contain the survey link. The reminders will include an option to cease receiving communications from Flinders NT.

We will also advertise the research on our social media sites (ie, Facebook, blog page, and website) in order to maximize exposure of potential participants to the study. This advertising will not contain a link to the survey but will simply describe the study and invite potential former placement students to contact us if they have not received an email invitation to participate.

To summarize, participants will be recruited in one of two ways, depending on their year of NT student placement:

Cohorts 1 and 2, which include health professional students known to have undertaken a Flinders NT–supported work-integrated placement during 2017 or 2018, will be contacted via their last recorded email address or phone number and invited to participate.Cohorts 3 to 12, which include health professional students undertaking Flinders NT–supported work-integrated placements from January 2019 and onward, will be emailed an invitation to participate at the conclusion of their placement.

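### Table 1 stops Survey 2 early for Cohorts 1, 2 and 4 and gives no end year for Cohort 3, so no cohort is shown to reach the tenth year in the primary objective

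*Protocol article*

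**What the plan says.** Research Question and Objectives sets annual identification of workplace location as the primary objective and adds that "this will be conducted for 10 years postgraduation".

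Table 1 (Theoretical Framework and Study Design) gives the survey calendar:
- Cohorts 1-3 (2017-2019 placements) start Survey 2 in 2020. The 2023-2028 column reads "Survey 2 taken annually up to and including 2026 for Cohort 1 and up to and including 2027 for Cohort 2". No end year is given for Cohort 3, and the shared row is marked as finished in 2029.
- Cohort 4 (2020 placements) starts in 2021, with "Survey 2 taken annually up to and including 2028".
- Cohorts 5-11 run to 2029 and are given 8, 7, 6, 5, 4, 3 and 2 workforce years. Cohort 12 has one Work Location Survey, in 2029.

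Footnote b says "Note that 2.1 refers to participants’ first year in the workforce or postgraduation, 2.2 is their second year, etc", and then "Participation ends after 10 years in the workforce or postgraduation".

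Sample Size takes 450 students a year, a response of 15% in the first year falling by one point a year to 6% in the tenth, a pool of 5400 "who will each be offered up to 10 surveys" depending on when they joined, and a final sample of 3175.

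Table 1 treats Cohort 3 as retrospectively recruited in 2020. Participant Recruitment puts Cohort 3 with the later cohorts, whose students on "work-integrated placements from January 2019 and onward, will be emailed an invitation to participate at the conclusion of their placement".

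**The concern.** The objective states a ten-year horizon without qualification, yet the printed stop years appear to fall short of it even for the earliest cohorts. With a fixed end in 2029, only Cohorts 1-3 can supply year-10 data. The Discussion names work location in the short, medium and long term as an open question, and these are the cohorts that can answer its long end. Ending them a year early would remove year 10 while the study is still in the field. The ethics approval runs to December 31, 2029. Survey 2 asks for work history, which can recover 2018-2019 for Cohorts 1 and 2, but nothing recovers years after the last survey.

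**Working it through.** **Step 1: the table's counting rule.** Years tracked = last survey year − placement year, with workforce year 1 being the year after placement. Cohort 5: 2029 − 2021 = 8, as stated. Cohorts 6-11 (placements 2022-2027): 7, 6, 5, 4, 3, 2, all as stated. The rule reproduces all seven printed figures.

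**Step 2: the same rule for Cohorts 1-4.** Surveys are counted from 2020 for Cohorts 1-3 and from 2021 for Cohort 4.

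| Cohort | Placement | Last Survey 2 | Workforce year reached | Survey 2 waves | Year 10 falls in |
|---|---|---|---|---|---|
| 1 | 2017 | 2026 | 9 | 7 | 2027 |
| 2 | 2018 | 2027 | 9 | 8 | 2028 |
| 3 | 2019 | 2028 (inferred) | 9 | 9 | 2029 |
| 4 | 2020 | 2028 | 8 | 8 | 2030 |

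On footnote b's literal numbering, with Survey 2.1 in 2020 as the first workforce year, Cohorts 1-3 end at 2.7, 2.8 and 2.9. Neither count reaches 10. Cohort 4 cannot reach year 10 by 2029, but it could reach year 9.

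**Step 3: the sample size.** The first-year figure reproduces: 3 × 450 × 15% = 202.5 (203 stated). So does the pool: 12 × 450 = 5400. With the rate falling by calendar year and no cohort ever stopped:

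1350 × 15% + 1800 × 14% + 2250 × 13% + … + 4950 × 7% + 5400 × 6% = 3172.5, against 3175 stated.

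Table 1's stops remove these waves:
- Cohort 1, 2027-2029: 450 × (8% + 7% + 6%) = 94.5
- Cohort 2, 2028-2029: 450 × (7% + 6%) = 58.5
- Cohort 3, 2029 (inferred): 450 × 6% = 27
- Cohort 4, 2029: 450 × 6% = 27

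The total removed is 207, and 3172.5 − 207 = 2965.5, about 6.6% below 3175. These are counts of survey responses, not of distinct people.

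**Step 4: expected responses by year after placement, at the same rates.**
- Year 8 (Cohorts 1-5, in 2025-2029): 450 × (10% + 9% + 8% + 7% + 6%) = 180
- Year 9 (Cohorts 1-3, in 2026-2028): 450 × (9% + 8% + 7%) = 108
- Year 10: 0

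With Cohorts 1-3 run to 2027, 2028 and 2029, and Cohort 4 to 2029:
- Year 9: 108 + 450 × 6% = 135
- Year 10: 450 × (8% + 7% + 6%) = 94.5
- Added responses: 94.5 + 27 = 121.5, for a total of 2965.5 + 121.5 = 3087
- 95% half-width for a proportion of 50% at year 10: 1.96 × √(0.25 / 94.5) = 0.101, about 10 points

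**The case against.** The strongest defence is that this is a labelling slip. Counting the placement year as year 1, 2017-2026 and 2018-2027 are each ten calendar years. But a placement year is not a postgraduation year, and this count contradicts the 8 years printed for Cohort 5. Nor does it explain Cohort 4, where 2020-2028 is nine years even so. It may well be how the stop years arose, but they still need reconciling.

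Several stronger readings are tempting, and the documents do not support them:
- *That the offer of up to 10 surveys is contradicted.* Sample Size does not say Work Location Surveys, and Participant Recruitment calls Survey 1 the first survey. Survey 1 plus nine Survey 2 waves for Cohort 3 makes ten.
- *That footnote b is breached.* It reads naturally as a cap, which shorter follow-up does not break.
- *That it is established that nobody reaches year 10.* Cohort 3's 2028 end is inferred from a cell shared by three cohorts. If Cohort 3 were surveyed in 2029, it alone would reach year 10.
- *That the shorter follow-up of Cohorts 5-12 is a hidden defect.* Table 1 prints it openly, and it follows from rolling recruitment with a fixed end.

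Two further points stand. The count runs from placement, whereas the objective counts from graduation, and no graduation dates are given; later graduation only shortens postgraduation follow-up. The article also specifies no year-10 estimate or test, and the 121 or so responses gained are about 4% of the 2965.5 expected under Table 1. The gain lies in having any year-10 data, not in the overall total.

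**Conclusion.** The point holds as an inconsistency between the schedule and the objective. Cohorts 1 and 2 stop at workforce year 9 and Cohort 4 at year 8, so the unqualified ten-year objective does not match Table 1, and as scheduled no cohort is shown to reach year 10. The missed year is avoidable for Cohorts 1-3 within the existing study dates. Table 1 and Sample Size also describe different schedules: about 2966 responses against 3175.

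This rests on three assumptions: workforce year 1 is the year after placement, as the table's own figures require; Cohort 3's last survey is in 2028; and the response rate falls by calendar year, the reading that comes within rounding of 3175. If Cohort 3 is in fact surveyed in 2029, the expected total is 2965.5 + 27 = 2992.5 and year 10 has about 27 responses rather than none. The mismatch for Cohorts 1, 2 and 4 is unchanged.

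The disagreement over how Cohort 3 is recruited is real but separate, and it does not bear on the length of follow-up.

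**What to change.** 1. In Table 1, run Survey 2 at least to 2027 for Cohort 1, 2028 for Cohort 2, and 2029 for Cohorts 3 and 4. Alternatively, run all four to 2029, which matches the 3175 and leaves room for graduation after the placement year. That option takes Cohorts 1 and 2 to years 12 and 11 after placement, so footnote b would have to say from which date its ten-year cap runs.
2. State Cohort 3's end year, and place it in one recruitment group in both Table 1 and Participant Recruitment.
3. Reword the primary objective as annually for up to 10 years, to 2029. Give each cohort's maximum follow-up, counted from the year after placement and not described as years since graduation: under the minimum change, 10 for Cohorts 1-3, 9 for Cohort 4, then 8 falling to 1 for Cohorts 5-12. Say that year-10 results come from Cohorts 1-3 only.
4. Bring the expected number of responses into line with the chosen schedule: about 3087 for the minimum change, or 3172.5 if all cohorts run to 2029.

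The minimum change costs four extra cohort-waves: 4 × 450 = 1,800 invitations, or up to 5,400 emails with the two planned reminders. Running all four cohorts to 2029 costs seven (3 + 2 + 1 + 1): 3,150 invitations, or up to 9,450 emails. Both fit the current study dates and ethics approval period.

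If the stop years are kept, restate the objective as up to 9 years, confirm 2028 as Cohort 3's end year, and give about 2966 as the expected number of responses.

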### Participants and Eligibility

Study participants will be students or graduates, over the age of 18 years, of an Australian allied health or nursing training program and will have undertaken an NT placement as a student. Their placement, including any assessment of competence, will be concluded by the time of participation. Individuals who were already employed as a nursing or allied health professional and undertaking a placement as part of a postgraduate qualification will be excluded.

Framed by our pragmatist approach and as part of our due diligence around appropriate research designs, we considered using Australian Health Practitioner Regulation Agency (AHPRA) registration data rather than participant survey data. However, only about half of the professions of interest are registered through the AHPRA: Aboriginal and Torres Strait Islander Health Practitioner, Chinese medicine, chiropractic, dentistry, medical radiation, nursing and midwifery, occupational therapy, optometry, osteopathy, pharmacy, physiotherapy, podiatry, and psychology. Disciplines that are not registered include audiology, dietetics and nutrition, disability, exercise physiology, medical laboratory science, orthotics and prosthetics, paramedicine, social work, and speech pathology. Therefore, relying on AHPRA data to answer our primary question will not provide coverage of all the professions of interest.

The research design relies on access to the contact details of health professional students known to have undertaken work-integrated learning placements in the NT from 2017 onward. Flinders NT holds a secure database with the contact details of the placement students. These details were obtained for the purpose of supporting the placement; however, students consent to the use of their information for educational research purposes, such as our standard quality-improvement Student Satisfaction Survey regarding placement. Access to the database will allow the researchers to recruit participants to the study by contacting current and former students and inviting them to participate in the research.

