### Outcomes

The primary outcome of the study is the workplace location, assessed using the Modified Monash Model (MMM) [47], with MMM 4 and 5 considered rural and MMM 6 and 7 considered remote. The MMM defines whether a location is urban, rural, remote, or very remote, based on the Australian Statistical Geography Standard—Remoteness Areas (ASGS-RA) framework. The model measures remoteness and population size on an MMM category scale, ranging from MMM 1 to MMM 7. MMM 1 is a major city and MMM 7 is very remote. Any health service provision in areas classified as MMM 4 to 7, whether full time or part time, in the previous 12 months will be considered a rural or remote workplace location.

Baseline data (ie, Survey 1: Student Satisfaction Survey) will be collected following student placements and will include age, gender, degree program in which student is enrolled, length of placement, placement location, Indigenous status, NT residency, and rural origin.

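### Survey 2 waves are labelled by year since graduation but scheduled from the placement, so the wave called 2.1 mixes career stages

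*Protocol article*

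**What the plan says.** All references are to the Protocol article.

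- **Research Question and Objectives:** the primary objective is annual workplace location over ten years, counted from graduation.
- **Table 1, footnote b:** the wave number is a career year: "2.1 refers to participants’ first year in the workforce or postgraduation, 2.2 is their second year, etc". The footnote ends participation after ten such years.
- **Participant Recruitment:** the first Work Location Survey is triggered by Survey 1, not by graduation: "The following year, Survey 2 (ie, the Work Location Survey) is sent". Under Outcomes, Survey 1 data "will be collected following student placements", so the chain starts at the placement.
- **Table 1, first row:** three placement years are pooled ("Retrospective recruitment of 2017-2019 students (Cohorts 1-3"). The 2020 cell reads "already undertaken as part of routine quality assurance Survey 2.1", so all three cohorts get 2.1 in the same year. The end dates then differ: "Survey 2 taken annually up to and including 2026 for Cohort 1 and up to and including 2027 for Cohort 2".
- **Participants and Eligibility:** entry is not limited to graduates: "Study participants will be students or graduates, over the age of 18 years". The Background says that placements are part of training throughout these programs, and no section restricts entry to final-year placements.

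**The concern.** The wave number is the only time index that the article defines, and it has two incompatible meanings. By the footnote it is years since graduation or workforce entry. By the schedule it is a count of surveys that starts the year after the placement, or in 2020 for all three retrospective cohorts. The two agree only for someone who graduates in the year before the first Survey 2, and nothing in the article ensures that.

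The primary objective is on a postgraduation scale, and the Discussion asks what proportion work remotely in the short, medium and long term after graduation. If results were tabulated by survey number, a figure presented as the first postgraduation year would combine people up to three years out with people who may still be studying. A trend over waves would also confound career stage with cohort.

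**Working it through.** **1. Which clock does Table 1 use?** If 2.1 falls in placement year + 1 and follow-up ends in 2029, the number of years tracked is 2029 − placement year.

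| Cohort | Placement year | 2029 − placement year | Workforce years stated in Table 1 |
|---|---|---|---|
| 5 | 2021 | 8 | 8 |
| 6 | 2022 | 7 | 7 |
| 7 | 2023 | 6 | 6 |
| 8 | 2024 | 5 | 5 |
| 9 | 2025 | 4 | 4 |
| 10 | 2026 | 3 | 3 |
| 11 | 2027 | 2 | 2 |

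All seven stated figures are reproduced. What the table calls workforce years are years since placement.

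**2. Do the end dates fit the footnote?** Cohort 1 runs from 2020 to 2026, which is 2026 − 2020 + 1 = 7 waves, ending at 2.7. Cohort 2 runs from 2020 to 2027, which is 8 waves, ending at 2.8. Neither reaches a tenth wave. Both end dates fall in the tenth calendar year counted inclusively from the placement (2017 to 2026 and 2018 to 2027). This again points to a placement clock for these two cohorts. Cohort 4, from 2021 to 2028, has 8 waves and ends in the ninth calendar year from placement, so it fits neither rule.

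**3. What postgraduation year is the wave labelled 2.1?** Let g be the whole years from placement to graduation. The documents do not give g; 0 to 3 is assumed.

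Postgraduation year at 2.1 = survey year − placement year − g

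| Cohort | Placement | Year of 2.1 | g = 0 | g = 1 | g = 2 | g = 3 |
|---|---|---|---|---|---|---|
| 1 | 2017 | 2020 | 3 | 2 | 1 | 0 |
| 2 | 2018 | 2020 | 2 | 1 | 0 | −1 |
| 3 to 12 | 2019 to 2028 | placement + 1 | 1 | 0 | −1 | −2 |

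Zero or below means not yet in a first postgraduation year.

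**4. How many are mislabelled?** Sample Size assumes 450 students per cohort, so Cohorts 1 to 3 give 3 × 450 = 1350 invitees in 2020. With g = 0 for everyone, Cohorts 1 and 2 are mislabelled: 900/1350 = 67%. Over all twelve cohorts this is 900/5400 = 17%. At the stated 15% response, 1350 × 0.15 = 202.5, which reproduces the plan's 203. Two thirds of that is 135 respondents, if response is equal across cohorts.

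The 67% does not depend on final-year placement. In 2020 the label is right only if g = 2 (Cohort 1), 1 (Cohort 2) or 0 (Cohort 3). If the three cohorts share one distribution of g with probabilities p0, p1, p2 and so on, the correctly labelled share is (p0 + p1 + p2)/3, which is at most one third.

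**5. How might the later cohorts add to this?** Suppose a share f graduates one year after the placement year and the rest in the placement year (an assumption). Of all 2.1 invitations, the mislabelled share is [1 + (1 − f) + 10f]/12 = (2 + 9f)/12. The share not yet in a first postgraduation year is 10f/12.

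| f (assumed) | Mislabelled | Not yet in first postgraduation year |
|---|---|---|
| 0 | 17% | 0% |
| 25% | 35% | 21% |
| 50% | 54% | 42% |
| 75% | 73% | 63% |

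These rows show only how sensitive the label is. They do not estimate the study population.

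**The case against.** The strongest reply is that a wrong label need not produce a wrong result. Data Analysis plans descriptive summaries, changes in work location and a logistic regression of MMM 4 to 7 against MMM 1 to 3, and indexes none of them by wave number. How waves map to analysis time is often settled in a fuller document that is not shown. The different end years for Cohorts 1 and 2 show that the planners were thinking of elapsed time. Participant Recruitment says that Survey 2 asks for work location history, so earlier years may be recoverable. The questionnaire is not reproduced and may already ask for graduation date. The eligibility wording describes who may enrol, not who receives each wave. All of this stands as a limit on the consequence.

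Two stronger readings should be resisted.

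- **Non-graduates are counted as not working remotely.** A reader might infer, for example, that a true 50% would be read as 0.50 × 0.80 = 40% or 0.50 × 0.60 = 30% if 20% to 40% of respondents had not graduated. The documents give no such share and no rule that scores a person without a health workplace as MMM 1 to 3 or keeps that person in the denominator.
- **Graduation date is not collected.** The baseline list under Outcomes omits it, but that list covers Survey 1 only.

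The reply does not remove the contradiction. The article states one time index, it disagrees with the article's own schedule, and nothing shown delays Survey 2 until graduation.

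**Conclusion.** The point holds as an internal contradiction about the time scale. Footnote b counts from graduation or workforce entry; Participant Recruitment and Table 1 count from the placement. If everyone graduated in the placement year, the labels for Cohorts 1 and 2 are off by two years and one year. The two-thirds error in the 2020 wave holds more widely, provided the three cohorts share a placement-to-graduation pattern.

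That current students answer 2.1 in any cohort is plausible from the eligibility rule and from placements occurring throughout training, but their number is unknown. The documents do not show that the analysis will use survey number, so a biased primary result is not established and its size cannot be calculated. What is established is that any result reported by survey number would mix career stages and would not answer the primary objective on its own scale.

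**What to change.** 1. Record graduation month and year (or expected date) and current student status in Survey 2, if these are not already asked.
2. Define analysis time as years since graduation and use survey number only as an administrative label.
3. Report responses given before graduation separately, outside the work-location denominator.
4. Use the existing work-history questions to fill the earlier postgraduation years for Cohorts 1 and 2, and mark these as recalled.
5. Reconcile footnote b with Table 1, including the workforce-year counts and the end years for Cohorts 1, 2 and 4. State an end year for Cohort 3, and place that cohort consistently: Table 1 treats it as retrospective, while Participant Recruitment groups it with Cohorts 4 to 12.

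The cost is about one added survey item, a re-derived time variable and a somewhat smaller denominator in the earliest years. It is cheaper early, since the plan expects response to fall from 15% to 6% and graduation dates will become harder to obtain.
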